#### Provision of technical assistance

We will provide bi-monthly technical support from the study team with assessment of fidelity and tailoring of the implementation strategy for 6 months at all sites. Depending on their wave assignment, sites will move to a maintenance phase of 18 (wave 1), 12 (wave 2), or 6 (wave 3) months of length as described in Fig. 1. Services provided during the intervention phase include bi-monthly supervision, data collection support, equipment and supplies related to the intervention, and ongoing clinical training for new staff. After the intervention phase bi-monthly, supervision is no longer provided but we will offer intermittent training where necessary and continue data collection. In Aim 2, reproductive health clinics will implement the intervention with the implementation strategy developed and refined at the year 1 stakeholder meeting. We expect that implementation strategies across the 10 sites will include some common and some site-specific components. During the 6-month intervention period, facilities will be supported by the study team to iteratively tailor their implementation strategy using their IRLM conceptual map and identified and prioritized strategy components. Any subsequent adaptations to the site-specific implementation strategies during the intervention period will be documented through use of the FRAME-IS tool [33] including collation of what is modified, the timing of the modification, and the actors and action targets of the modification.

#### Formation of facility committees

We will convene a committee that will serve an advisory team at the facility level. This committee will work closely with the research team to provide input on on-project implementation processes and receive updates provided by the research team. The research team will liaise with the committees to schedule regularly scheduled meetings. We will evaluate the impact of the intervention on the clinical and implementation outcomes using the RE-AIM framework (Table 1).

**Table 1 Tab1:** Summary of outcomes, by RE-AIM domain

RE-AIM domain	Outcomes	Data source
**Reach**	• Proportion of providers trained and women screened per month	• Abstracted client records • Facility level data
**Effectiveness**	• Number of women screen-positive per month • Treatment completion rate among screen-positive women compared to pre-intervention (primary) • Proportion of women with clearance of HPV 6 months post-receiving TA treatment	• Facility level data • HPV test results from randomly selected women
**Adoption**	• Proportion of selected clinics incorporating thermal ablation into routine care through updated policies • Proportion of trained providers performing SV-SAT + TA • Facility readiness	• Facility level data, Technical assistance reports • ORIC scores
**Implementation**	• Core components of the SV-SAT + TA • Description of drivers of success/failure using CFIR constructs of interest	• Facility level data, Technical assistance reports • Key informant interviews
**Maintenance**	• Proportion of clinics that continue to provide and sustain SV-SAT + TA services 12,18, and 24 months after intervention implementation	• Facility level data

### REACH

For reach of the intervention, we will assess the number of providers trained within each clinic. We hypothesize that the intervention will increase the number of women receiving cervical cancer screening and treatment services in all facilities. We will abstract program data and estimate the number of women aged 25–49 years (according to the Kenyan national screening guidelines) seeking services in reproductive health clinics who are screened per month [34].

### Effectiveness

We will assess effectiveness by determining whether the intervention is associated with an increase in the number of screen-positive women identified per month and proportion of screen-positive women who complete treatment (target = 60%) comparing pre-implementation period to intervention periods. This will include women treated with thermal ablation, cryotherapy, LEEP, or any other procedure.

#### Data analysis

The primary analysis will be an individual level analysis comparing the primary efficacy outcome (probability of screen-positive women being treated the same day) pre- vs post-intervention. We will estimate differences using weighted least square methods appropriate for this facility-randomized three-wave stepped-wedge design, where all clinics begin in the control condition. We will consider the intervention effect to be fixed throughout the post-intervention period, but random intercepts per facility and wave. Within the post-intervention period, we will examine whether the effect waned in the maintenance phase using an analysis comparing the intensive vs maintenance phases. To analyze secondary outcomes of probability of providers being trained and number of women screened (REACH outcomes) and number screen-positive (secondary efficacy outcome), we will use the same analysis approach. Exploratory analysis will examine potential effect modification of facility-level factors such as patient volume, patient to provider ratio, and women screened. Potential multi-level adjustment variables include individual-level factors such as age.

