### Maintenance

In the first 6 months of implementation in each wave, we will have bi-monthly on-going technical support to health facilities. Thereafter, we will reduce visits to once a month among clinics that meet metrics for transition, and we will then discontinue routine technical assistance visits, but only respond to facility requests as needed. Over this time, research staff will continue to abstract individual level programmatic data. We will continue to monitor the proportion of screen-positive women who complete treatment. In addition, we will monitor the frequency of facility committee meetings. We anticipate that facilities will continue to implement the intervention because we will have utilized a participatory approach that builds ownership and organizational commitment and results in implementation of an intervention that is contextually fit.

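### One constant effect across the intensive and maintenance phases leaves the meaning of the primary estimate to how calendar time is modelled, if the effect wanes

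*Protocol article*

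**What the plan says.** The Data analysis section sets the primary contrast as "comparing the primary efficacy outcome (probability of screen-positive women being treated the same day) pre- vs post-intervention", to be estimated by "weighted least square methods appropriate for this facility-randomized three-wave stepped-wedge design, where all clinics begin in the control condition". The model is: "We will consider the intervention effect to be fixed throughout the post-intervention period", with random intercepts for facility and for wave. Waning gets a separate analysis restricted to exposed time: "Within the post-intervention period, we will examine whether the effect waned in the maintenance phase", by setting the intensive phase against the maintenance phase.

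Provision of technical assistance gives each clinic 6 months of intensive support, after which "sites will move to a maintenance phase of 18 (wave 1), 12 (wave 2), or 6 (wave 3) months of length". Regular supervision then ends, while occasional training and data collection go on. The Maintenance section describes the step-down differently: after 6 months "we will reduce visits to once a month among clinics that meet metrics for transition", followed by help on request only.

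No calendar-period term is named for either analysis. The random intercept for *wave* could mean the 6-month period or the randomised group of clinics, and the text does not say which.

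**The concern.** A constant effect is a modelling assumption, and this design gives a specific reason to doubt it: the level of support changes at month 6 in every clinic. The plan acknowledges this by looking for waning, but keeps the constant effect for the headline result.

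In a stepped wedge, a constant-effect model does not weight exposed time in proportion to how much of it there is. The weights follow from the covariance and calendar-time terms, and some can be negative. If the effect changes with time since crossover, the single coefficient may describe only the first 6 months, or an average contaminated by secular trend. The trial is about sustainable services, so a reader would naturally take the headline as the benefit over the whole post-intervention period.

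The separate waning analysis raises a related question. Within a clinic, maintenance always follows the intensive phase, so a secular rise can hide waning if calendar time is left out.

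**Working it through.** **Inputs from the article.** Ten clinics in three 6-month waves of three to four clinics (Aim 2 overview). Maintenance of 18, 12 or 6 months (Provision of technical assistance). At least 6 months of baseline data (Data collection and abstraction). An average of 9 screen-positive women per clinic per wave, ICC 0.2, alpha 0.05, 20% versus 60% (Power and sample size).

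**Assumptions.** Split 3/3/4; one baseline period, so five 6-month periods; linear probability scale; two-sided test; residual variance 0.24 (= 0.6 × 0.4); clinic variance 0.06, since 0.06/(0.06 + 0.24) = 0.2. A clinic-period mean has residual variance 0.24/9.

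**The plan's own figure.** Generalised least squares on clinic-period means, with a random clinic intercept, fixed period effects and one constant effect, gives SE 0.0908. Power is Φ(0.40/0.0908 − 1.96) = 0.993 (0.988 with four periods), so the stated 80% is not reproduced. It appears only with inputs that the article does not state, such as a low cluster autocorrelation or a large random treatment effect. This is a side observation and does not decide the point.

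**Exposed time.** Intensive: 10 clinic-periods. Maintenance: 3×3 + 3×2 + 4×1 = 19. Total 29, of which 66% is maintenance. By 6-month interval since crossover the counts are 10, 10, 6 and 3.

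**Weights of the constant-effect estimator by interval since crossover**

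| Calendar-time term | 0–6 | 6–12 | 12–18 | 18–24 | All maintenance |
|---|---|---|---|---|---|
| Fixed periods | 1.021 | 0.371 | −0.205 | −0.188 | −0.02 |
| Random period, variance 0.001 | 0.45 | 0.38 | 0.13 | 0.04 | 0.55 |
| None | 0.39 | 0.39 | 0.17 | 0.06 | 0.61 |

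**Expected estimate (weights × true effects, in points)**

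| True effect by interval | Mean over exposed clinic-periods | Fixed periods | No period term |
|---|---|---|---|
| 40, then 20 | (400 + 380)/29 = 26.9 | 40.4 | 27.7 |
| 40, then 0 | 400/29 = 13.8 | 40.8 | 15.4 |
| 40/30/20/10 | (400 + 300 + 120 + 30)/29 = 29.3 | 46.0 | 31 |

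For the last row with fixed periods: 1.021×40 + 0.371×30 − 0.205×20 − 0.188×10 = 40.84 + 11.13 − 4.10 − 1.88 = 46.0, which is above every true effect. With no period term, a secular rise of 5 points per period adds 12.4 points to the primary estimate.

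**Post-only waning comparison.** In the four post-rollout periods the intensive clinics number 3, 3, 4, 0 and the maintenance clinics 0, 3, 6, 10. Both phases run side by side in two periods. With period effects the design has full rank, trend bias is 0 and the SE is 0.104. Without them, a trend of +3 or +5 points per period biases maintenance minus intensive by +4.4 or +7.4 points, which masks waning. A falling trend exaggerates it by the same amount.

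**Two-phase model on all data with fixed periods.** SE 0.091 for the intensive effect, 0.130 for the maintenance effect and 0.091 for their difference. Power for a 20-point drop is Φ(0.20/0.091 − 1.96) ≈ 59%, against about 49% post-only with periods. Under gradual 40/30/20/10 waning this model is itself biased: it returns 45.8 and 38.0, where the true values are 40 and 450/19 = 23.7.

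**The case against.** The strongest reply is that the alarming figures need fixed period effects, which the article does not state; it names random intercepts. With no period term, or a random one of small variance, all weights are positive and the estimate lies near the exposed-period mean. Even with fixed periods, under a step drop the estimate can be read as the intensive-phase effect. The waning comparison is prespecified and treatment completion continues to be monitored, so a drop would be looked for. The analysis plan may also settle the period term.

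Much of this stands, and it limits the point.

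- A reader might infer that the primary estimate is uninterpretable in general. It is not: the difficulty arises under waning, and its form depends on the calendar-time term. With zero cluster autocorrelation the fixed-period weights are 0.73, 0.27, 0 and 0, with none negative.
- A reader might infer that the waning comparison confounds phase with calendar time by design. The staggered starts rule that out; bias arises only if period is omitted.
- A reader might infer that maintenance is unsupported. The article describes reduced help: occasional training, monthly visits for some clinics and response to requests.
- A two-phase model is no complete cure, as its bias under gradual waning shows. Which phase to headline is the investigators' choice.

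What the reply does not remove is that the constant effect is a stated choice, not an omitted detail. The models with little period adjustment escape negative weights only by giving up protection against secular trend. A random period effect of variance 0.01 still puts 0.72 on the intensive phase and negative weight after month 12.

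**Conclusion.** The point holds as a worthwhile, inexpensive improvement. The article fixes one effect over two levels of support and does not clearly specify the term that decides what this effect means under waning. With fixed periods the estimate is almost wholly the intensive-phase effect: 40.8 points where the exposed-period mean is 13.8, and 46 under gradual waning. Without period terms it is near the mean, but takes up 12.4 points from a secular rise of 5 points per period. The waning comparison is sound if period is included and off by 4.4 or 7.4 points under trends of 3 or 5 points per period if it is not.

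These figures rest on the assumed waning and trend patterns, five equal periods and the variances given above. Splits of 4/3/3 and 3/4/3 give a similar picture (fixed-period intensive weight 1.02 to 1.07). If the effect does not wane, the constant model has no such problem.

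The two descriptions of how support steps down also differ. A reader might infer that phase will depend on clinic performance. That would follow only if phase were classified by support received, which the article does not say.

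**What to change.** 1. In the full-data model, keep the control periods and fixed calendar-period effects, and replace the single indicator with two: intensive (months 1–6 after crossover) and maintenance (month 7 on). State which effect, or which average of the two, is primary.
2. Test waning as the difference of the two coefficients in that model, in place of the post-only comparison.
3. Add a sensitivity analysis with one effect per 6-month interval since crossover, because the two-phase model is biased under gradual waning.
4. Define phase by months since crossover for every clinic, whatever support it received. Say whether *wave* in the model means period or randomised group.
5. Reconcile the Provision of technical assistance and Maintenance sections on when and how support steps down.

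**Cost.** One extra model term and no new data. Relative to a constant effect with fixed periods, the intensive-effect SE stays at about 0.091 (about 0.101 with exposure-time effects). It is larger than the 0.05 to 0.055 of a model with no or weak period adjustment; that is the price of protection against trend. The maintenance effect is less precise, with SE 0.130. The SE of the waning contrast improves from 0.104 (post-only with periods) to 0.091.

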In the SV-SAT approach, women who screen positive for precancerous lesions are immediately treated with ablative therapy such as cryotherapy or thermal ablation, which minimizes loss to follow-up or attrition of screen-positive women [17, 18]. According to the 2015 Kenya STEPwise survey report on non-communicable diseases [5], up to 70% of screen-positive women do not receive treatment [19]. Low fidelity of the SV-SAT approach and treatment with cryotherapy in Kenya has been attributed to programmatic and logistical challenges of implementing cryotherapy in low-resource settings [15]. For example, large tanks of compressed refrigerant gas are difficult to supply and transport consistently to remote areas [14, 15, 20]. The equipment (cryotherapy probe and gas) is costly, and clinics that maintain cryotherapy equipment in Kenya have reported challenges with equipment failure and high turnover of trained personnel [21]. The 2019 WHO recommendations have added thermal ablation as another ablative treatment method for precancerous lesions [22]. The portable thermal ablation device can be charged with electricity, batteries, or solar panels, which is ideal for low-resource settings [23]. While the safety, efficacy, and acceptability of thermal ablation to women has been demonstrated in limited settings in parts of Zambia and Kenya [20, 24, 25], the drivers of its implementation and scale-up have not been determined.

Implementation strategies of evidence-based interventions (EBIs) such as SV-SAT with VIA and thermal ablation can facilitate identification of multi-level determinants of cervical cancer screening and treatment uptake and tailor EBIs to the local contexts to enhance their adoption and sustainment. We hypothesize that this intervention, along with tailored implementation strategies, will enhance the adoption and sustainability of cervical cancer screening and treatment compared to the standard of care using cryotherapy. Our specific aims are to:

Aim 1) Develop locally tailored implementation strategies using multi-level participatory method with key stakeholders (patient, provider, system-level)Aim 2) Implement the intervention and evaluate clinical and implementation outcomes using the RE-AIM framework.Aim 3) Assess the budget impact of the intervention compared to single-visit, screen-and-treat method using cryotherapy.

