### Randomization

Three to four clinics will be randomly assigned to one of three 6-month implementation waves at the stakeholder meeting at the conclusion of year 1. The clinics will be stratified by size.

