### Aim 2: implement the intervention and evaluate clinical and implementation outcomes using the RE-AIM framework

#### Overview

At 10 reproductive health clinics in central Kenya, we will introduce the intervention and site-specific implementation strategy developed in Aim 1 in a stepped-wedge fashion and rigorously evaluate how effectively this strategy is disseminated and implemented. In three successive 6-month waves, we will roll out the intervention at three to four clinics. A maintenance phase of varying lengths will be conducted across all waves.

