#### Power and sample size

The stepped-wedge study design is powered based on the primary effectiveness outcome, which is the proportion of screen-positive women who receive same-day treatment. According to data on cervical cancer screening and preventive treatment for Kiambu county from 2017 to 2019, 20% of cervical cancer screening clients who screened positive received cryotherapy or LEEP. Routine data from our proposed study facilities show an average of 30 clients per month screened at each facility in the first 3 months of 2020. Assuming 6-month waves, 30 clients screened per month and a 5% screen positive rate, we expect an average of 9 screen-positive women per facility per wave. Assuming an intracluster correlation coefficient of 0.2, alpha = 0.05, and 20% treatment coverage pre-intervention, we will have 80% power to detect a three-fold increase to 60% treatment coverage with the intervention (R [v 3.6.3] package swCRTDesign [v 3.1]). We estimate that 90% of screen-positive women will be eligible for ablative treatment.

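### As worded, the primary model's random intercepts may leave out a clinic's own change between six-month periods; if clinics fluctuate, the standard error is then too small

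*Protocol article*

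**What the plan says.** The Data analysis section under Effectiveness sets the primary model. The level is the individual woman: "The primary analysis will be an individual level analysis comparing the primary efficacy outcome". The estimator is weighted least squares: "We will estimate differences using weighted least square methods appropriate for this facility-randomized three-wave stepped-wedge design". The random structure is: "We will consider the intervention effect to be fixed throughout the post-intervention period, but random intercepts per facility and wave".

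Wave carries two meanings in the article. In Randomization it is a group to which clinics are allocated: "Three to four clinics will be randomly assigned to one of three 6-month implementation waves". Provision of technical assistance also uses it this way, giving wave 1, 2 and 3 sites different maintenance lengths. In Power and sample size it is a length of time: the expected nine screen-positive women are counted for each facility in each six-month wave. That section gives one correlation and no between-period correlation: "Assuming an intracluster correlation coefficient of 0.2, alpha = 0.05, and 20% treatment coverage pre-intervention".

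**The concern.** The phrase has three possible readings:

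- an intercept for facility and one for rollout group;
- an intercept for facility and one for calendar period, shared by all clinics;
- an intercept for facility and one for each facility-by-period cell.

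Only the third lets a single clinic's treatment rate move between periods independently of the other clinics. On the first two, such movement is treated as binomial noise among individual women, which nine women per cell would average down. In fact it is shared by all women in the cell and does not average down.

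The article's own Background gives reasons to expect movement of this kind. It mentions supply stockouts and loss of trained staff, and says that clinics maintaining cryotherapy equipment have "reported challenges with equipment failure and high turnover of trained personnel". At stake are the significance level and the interval width of the primary comparison. The problem would be present even if the intervention had no effect at any clinic.

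**Working it through.** **Inputs from the article.** There are ten clinics (Overview: "At 10 reproductive health clinics in central Kenya, we will introduce the intervention") and three steps ("In three successive 6-month waves, we will roll out the intervention at three to four clinics"), taken as 3/3/4. Women per cell: 30 × 6 × 0.05 = 9, which reproduces the article's figure. ICC is 0.2, control rate 20%, alpha 0.05 (two-sided assumed). Periods: one baseline of at least six months, three waves, and the last wave's six-month maintenance, so 1 + 3 + 1 = 5.

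**Assumption.** CAC is not given, so it is varied from 1.0 (a clinic's level never changes) to 0.5.

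**The article's power figure.** A standard stepped-wedge calculation (facility intercept, fixed periods, normal approximation) gives 98.8-100% for 20% versus 60%, not 80%. About 80% appears only if a random treatment effect with roughly twice the facility variance is added, and the article states none. This is a separate matter. Here it shows only that there is power to spare.

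**Type I error without the facility-by-period term.** Binary outcomes, true rate 20% throughout, individual-level fit with facility intercept and fixed periods, 2,000 runs for each CAC:

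| CAC | mean model SE | actual SD of estimate | ratio | rejection, normal | rejection, t(8) |
|---|---|---|---|---|---|
| 1.0 | 0.065 | 0.066 | 0.985 | 5.4% | 2.3% |
| 0.9 | 0.066 | 0.074 | 0.892 | 7.4% | 3.8% |
| 0.8 | 0.066 | 0.079 | 0.835 | 10.0% | 5.1% |
| 0.7 | 0.067 | 0.085 | 0.788 | 13.0% | 6.6% |
| 0.5 | 0.068 | 0.096 | 0.708 | 15.8% | 10.2% |

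The ratio explains the rejection rates. At CAC 0.8 the effective cut-off is 1.96 × 0.835 = 1.64, with a two-sided normal tail of 10.2%. At CAC 0.5 it is 1.96 × 0.708 = 1.39, with a tail of 16.5%. With the t(8) cut-off of 2.306 the same step gives 1.93 (5.4%) and 1.63 (10.2%).

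**The two readings fitted as worded** (700 runs each, so the simulation error is about one percentage point), at CAC 1.0, 0.8 and 0.5 with a normal reference:

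- facility plus shared random period: 4.7%, 8.0%, 13.3%;
- facility plus random rollout group: 6.1%, 9.6%, 13.6%.

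With t(8) the figures at 0.8 and 0.5 are 3.7% and 8.6% for the first, and 4.1% and 8.3% for the second.

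**With a facility-by-period intercept added.** Over CAC 1.0 to 0.5, rejection is 4.3-7.1% with a normal reference and 2-4% with t(8).

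**Weighted least squares on facility-period means**, with the residual variance estimated: 5-7% with a normal reference. The extra variation goes into the residual.

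**Power with the added term.** With the variance taken at 40%, the midpoint of 20% and 60%, the standard error is 0.081 at CAC 1.0, 0.097 at 0.8 and 0.114 at 0.5.

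- Normal reference: 0.40/0.097 − 1.96 = 2.16, power about 98%; 0.40/0.114 − 1.96 = 1.55, about 94%. Across four or five periods the range is 93-98%.
- Cut-off of 2.306: 0.40/0.097 − 2.306 = 1.82, about 97%; 0.40/0.114 − 2.306 = 1.20, about 89%.

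**The case against.** The closest parallel to the disputed phrase is in Power and sample size, where the unit is plainly the facility in a given six-month wave. On that reading, with a facility intercept as well, the term is already present and nothing is wrong. This stands: the article supports saying that the wording is unclear, not that the term is certainly absent.

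A reader might infer that the test rejects a true null 10-15% of the time. The documents do not support that as a flat statement. It needs a CAC of about 0.8 to 0.5, which the article does not give, and a cut-off of 1.96, which it does not name. The Background evidence on stockouts and turnover is qualitative and not measured in these ten clinics. The reference distribution can properly be left to a fuller plan, so its absence is not a fault in itself.

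A reader might also say that the model makes two women at one clinic equally alike whatever the time between their visits. That is untrue for a shared random period intercept, which makes same-period women somewhat more alike. But that component is common to all clinics and does not capture one clinic's own swing.

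Finally, weighted least squares might be run on facility-period means, which would largely avoid the problem. The section says the analysis is at individual level, so this route is uncertain.

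The objections limit the size and certainty of the point. They do not remove the need to settle the wording, because the article itself fixes the random structure and two of its three readings share the weakness.

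**Conclusion.** The point holds in conditional form. On the rollout-group and shared-period readings, the individual-level primary model understates its standard error if clinics fluctuate between periods. With ten clinics, nine women per cell, ICC 0.2 and five periods, type I error with a normal reference is about 5-6% at CAC 1.0, 8-10% at 0.8 and 13-16% at 0.5. With t(8) it is about 2-4%, 5% and 9-10%, a little lower at 0.8 and 0.5 on the two readings fitted as worded. If the phrase means facility plus facility-by-period, there is no such defect. It would go too far to conclude that alpha is not held: that depends on the reading, on an unknown CAC and on an unnamed reference distribution. At the target difference of 40 points the practical consequence is limited. It matters more if the observed effect is small.

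**What to change.** In Data analysis, replace the random-effects wording with: *random intercepts for facility and for facility-by-six-month period*. State a small-sample reference distribution, for example t with clusters minus 2 = 8 degrees of freedom, because the added term with a normal reference still gives about 4-7%. Use wave for one thing only, either rollout group or period.

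A randomisation test that re-draws the clinic allocation within the size strata can serve as a sensitivity analysis. It need not supply the primary p value.

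The cost is a wording change and a short program. The standard error widens if clinics do fluctuate (0.081 to 0.097 or 0.114 at CAC 0.8 or 0.5), and t(8) is somewhat conservative (2-4%). Power stays above the stated 80% in every case shown.

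### The stated primary model names no fixed calendar-period effect and relies on an undefined random 'wave' intercept, so a secular trend is at best partly separated from the intervention effect

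*Protocol article*

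**What the plan says.** The Data analysis section (protocol article, Aim 2) defines the primary analysis as individual-level, "comparing the primary efficacy outcome (probability of screen-positive women being treated the same day) pre- vs post-intervention". On the estimator it says: "We will estimate differences using weighted least square methods appropriate for this facility-randomized three-wave stepped-wedge design". On the terms it says: "We will consider the intervention effect to be fixed throughout the post-intervention period, but random intercepts per facility and wave". The only adjustment named is optional: "Potential multi-level adjustment variables include individual-level factors such as age". The Effectiveness section repeats the before-after framing: "comparing pre-implementation period to intervention periods". No sentence names calendar time as a fixed effect.

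'Wave' is used in two senses. Randomization assigns clinics to one of three waves, and Provision of technical assistance gives maintenance lengths by wave assignment; there it is the start group. The Aim 2 Overview describes three successive 6-month waves, and Power and sample size counts women in time units: "we expect an average of 9 screen-positive women per facility per wave". There it is a calendar period. Data analysis does not say which sense applies in its "random intercepts per facility and wave".

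**The concern.** All clinics start in the control condition and cross over in one direction. Within each clinic every intervention month is therefore later than every control month. Any change in same-day treatment that would have happened anyway goes in the same direction as exposure. A stepped wedge separates the two by comparing clinics that have crossed over with clinics that have not, within the same calendar period. That requires the model to take out period differences.

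If it does not, the estimate mixes the intervention with time, its standard error is too small, and the type I error of the primary test is not controlled. The same approach is stated for the number screened, the number screen-positive and provider training. The reach and effectiveness results also feed the decision model in Aim 3.

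**Working it through.** **Inputs from the article.** 10 clinics, three to four per wave (3/3/4 used); at least 6 months of control data before the first start; 6-month waves; ICC 0.2; alpha 0.05 (two-sided assumed); 20% versus 60%. Women per clinic-period: 30 × 6 × 0.05 = 9, which reproduces the article's figure. If only the 90% eligible for ablation count, it is 8.1.

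**Periods.** Baseline plus three waves gives four. The maintenance lengths give five: wave 1 runs 6 + 18 = 24 months after the first start, wave 2 runs 6 + 6 + 12 = 24, wave 3 runs 12 + 6 + 6 = 24, and the 6-month baseline makes 30 months.

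**Assumptions.** A linear secular rise of *d* = 2 to 5 points per 6 months with no true effect. Total variance 0.4 × 0.6 = 0.24, split by the ICC into 0.048 between clinics and 0.192 within.

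**Step 1: by hand, wave as start group.** A clinic that starts at period *g* (periods numbered 0 to T − 1) has mean control time (g − 1)/2 and mean intervention time (g + T − 1)/2. The difference is T/2 periods for every start group. A within-clinic before-after contrast therefore picks up *d* × T/2:
- four periods: 2 × 2 = 4 and 2 × 5 = 10 points;
- five periods: 2.5 × 2 = 5 and 2.5 × 5 = 12.5 points.

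A random intercept for the start group is constant over time within a clinic, so it cannot reduce this.

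**Step 2: weighted least squares.** On clinic-period means the covariance is V = 0.048 J + (0.192/9) I within a clinic, plus a period variance shared by all clinics if period is random. The expected estimate is the intervention element of (D′V⁻¹D)⁻¹D′V⁻¹μ, where μ is the linear trend and D holds the fixed terms. Entries are the spurious effect in points, with the rejection rate from a normal reference in brackets.

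| Treatment of time | 4 periods, d = 2 | 4 periods, d = 5 | 5 periods, d = 2 | 5 periods, d = 5 |
|---|---|---|---|---|
| No period term (wave = start group) | 3.9 (12%) | 9.8 (50%) | 5.0 (20%) | 12.4 (80%) |
| Random period, SD 0.02 | 3.7 (11%) | 9.2 (41%) | 4.7 (17%) | 11.7 (70%) |
| Random period, SD 0.05 | 2.8 (7%) | 7.0 (20%) | 3.7 (10%) | 9.2 (37%) |
| Random period, SD 0.10 | 1.5 (5.5%) | 3.7 (8%) | 2.1 (6%) | 5.2 (12%) |
| Fixed period | 0 (5%) | 0 (5%) | 0 (5%) | 0 (5%) |

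Adding a start-group intercept with variance 0.01 to the first row moves it by less than 0.1 point.

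**Step 3: period variance estimated rather than assumed.** REML simulation, 300 runs per setting, no true effect:
- Four periods, *d* = 5: 9.6 points and 53% false positives with no period term; 6.7 points and 35% with random period; 0.2 points and 4% with fixed period.
- Five periods, *d* = 3: 7.0 points and 40% (start group); 5.7 points and 31% (random period); 0.1 points and 7% (fixed).
- Five periods, *d* = 5: 12.0 points and 80%; 8.3 points and 49%; −0.2 points and 5%.

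In these runs the random period absorbs 1 − 6.7/9.6 = 30%, 1 − 5.7/7.0 = 19% and 1 − 8.3/12.0 = 31% of the bias.

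**Step 4: cost in precision.** With variance 0.24 and 9 women, fixed periods raise the standard error from 0.050 to 0.085 (four periods) or from 0.044 to 0.081 (five). Power for a 0.40 difference is Φ(0.40/SE − 1.96): 0.40/0.085 − 1.96 = 2.75, about 99.7%. With total variance 0.20 to 0.24, 8.1 or 9 women, and a normal or t (8 df) reference, the range is about 97 to 99.9%. If 25 to 100% of the ICC lies in a facility-by-period component, it is about 89 to 99% (normal) or 79 to 96% (t, 8 df).

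The article's stated 80% power is not reproduced by the facility-intercept model, which gives more. That is a separate matter and bears neither way on this point.

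**The case against.** The strongest reply is that the article does not exclude period effects. It calls the estimator appropriate for a stepped wedge, does not say its list of terms is complete, and condenses a fuller protocol. A reader might infer that the model has no calendar adjustment; the text supports only that none is named as a fixed effect. This stands as a limit on the wording. It does not remove the point, because the article does choose to state which effects are fixed and which random, and the terms it lists leave bias under either meaning of 'wave'.

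A reader might also infer that any secular rise is counted in full as an intervention effect. That holds only for the start-group meaning. The time meaning is at least as natural, and then part of the rise is absorbed.

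Third, the trend is an assumption. The Background cites a national strategy that prioritises early detection, which concerns screening rather than same-day treatment of screen-positive women. A 5-point rise per period adds 4 × 5 = 20 points over five periods and would double the 20% baseline, so it is a severe case. The spurious effects are also small beside the planned 40-point difference. It would therefore be too strong to say that a trend alone would produce a positive trial: at 2 points per period the rejection rate is 5.5 to 20%. What remains is that the error rate is uncontrolled and depends on an unknown trend.

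Finally, Randomization stratifies by clinic size and the model does not list size. The facility intercept already takes up most stable size differences, so this is not part of the point.

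**Conclusion.** The point holds in a limited form. The stated primary model names no fixed calendar-period effect, and its random 'wave' intercept is undefined. On the terms listed, a secular trend is not separated from the intervention (start-group meaning) or only partly separated (period meaning). For an assumed rise of 2 to 5 points per 6 months and no true effect, the spurious effect is about 4 to 12 points in the first case and about 1.5 to 12 points in the second, where the size depends on the period variance. False positives run from just above 5% to about 80%. With fixed periods the bias is zero. These sizes rest on a linear trend common to all clinics, a 3/3/4 split, four or five periods, nine women per clinic-period and ICC 0.2. With no secular trend there is no bias.

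**What to change.** Define 'wave' once, and use separate words for the randomised start group and the 6-month calendar period. Replace the sentence on model terms with one stating that the primary model contains a fixed intervention effect, fixed categorical effects for each 6-month calendar period, and a random facility intercept. Carry the same terms to the outcomes that share this approach. A facility-by-period random effect and a small-sample reference (t on facility-based degrees of freedom, or permutation over the allocations that the randomisation allowed) are optional additions.

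The change is to wording only: routine data are abstracted monthly, so calendar period is already available. The price is the larger standard error shown above. With a facility intercept only, the stated 80% power is kept with room to spare. If both optional terms are added and all of the ICC lies in facility-by-period, power can fall to about 79%, so they should be chosen with that in view.
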